## 2.2 Number of participants required

Based on previous studies, we estimate the event rate at 12 months for the primary endpoint to be 30% for the intervention group and 40% for the control group. Assuming equally spaced enrollment and allocation, a total of 423 subjects would be needed for the analysis to have a power of 0.80 with a two-sided test at a significance level of 0.05. We estimate 15-20% exclusion from the analysis and plan to enroll a total of 500 subjects (250 in each group) over the 2-year period.

## 3. Analysis set

The analysis of the primary and secondary endpoints will include all study participants enrolled in the study. If it is found that the eligibility criteria are not met after the start of the study, they will be excluded from the analysis.

## 4. Data handling

### 4.1 Handling of missing data and outlier

#### Handling of missing data

In case of missing data, no imputation will be performed. However, if it is known before the data are fixed that there are missing values that may have a significant impact on the analysis results, methods to deal with the missing values will be described in this analysis plan.

#### Handling of outliers

In case of abnormal data, the analysis will be performed without excluding those values. However, if the presence of an outliers that may have a significant impact on the analysis results is known prior to data fixation, methods to deal with the outliers will be described in this analysis plan.

## 4.2 Allowance range of time-specific measurements

The allowance range listed in the schedule table on page 7 of the study protocol will be adopted.

## 4.3 Definition of endpoints

- Age is defined as the age at the time of admission.
- The unit of time in the analysis of this study is, in principle, handled in months.  
In this study, one month is approximately 30.4 ( $=365.25/12$ ) days, and if the acquired data are in dates, the conversion will be performed as follows

$$\text{Number of months} = \text{number of days} * 12 / 365.25$$

- Time to death, rehospitalization, and unscheduled visits

### Definition of time to death

The duration of time from the date of enrollment and random allocation to death from any cause.

### Definition of time to rehospitalization

The duration of time from the date of enrollment and random allocation to "rehospitalization for any new event". A transfer to a hospital is considered a continuation of hospitalization, thus will not be deemed as rehospitalization.

### Definition of time to unscheduled hospital visits

The duration of time from the date of enrollment and random allocation to "unscheduled hospital visit".

If two or more of these deaths, rehospitalizations, or unscheduled visits are confirmed, the shortest period of time for each is defined as the "time to death, rehospitalization, or unscheduled visit".

- Body Mass Index (BMI) is calculated based on the following formula  
$$\text{BMI (kg/m}^2\text{)} = \text{Weight (kg)} / \text{Height (m)} / \text{Height (m)}$$
- Time to death during initial hospitalization  
Time to death from any cause occurring during the initial hospitalization, starting from the date of enrollment and random allocation.

## 5. Definition related to statistical analysis

### 5.1 Definition related to statistical analysis methods

- Descriptive statistics for categorical data will be count and proportion for each category.

- Descriptive statistics for continuous data will be the number of persons, mean, standard deviation, median, 25th percentile, 75th percentile, minimum and maximum.
- Two-sided test with a significance level of 0.05 will be used for group comparison.

## 5.2 Number of digits displayed

- Proportions (%) are displayed to one decimal place.
- Mean, standard deviation, median, 25th percentile, 75th percentile, minimum, maximum, and confidence interval should be displayed one digit below the number of digits from the input data.

## 5.3 Software used for analysis

As a rule, use R version 4.0 or higher.

## 6. Classification of participants

### 6.1 Classification of participants

A flow diagram for the following items will be provided. The count and proportion of each item will be calculated.

[Classification]

Cases with consent, eligible cases, ineligible cases, enrolled cases, unenrolled cases, cases with completed follow-up, discontinued cases.

### 6.2 Discontinuation or dropout from the study

Subjects who discontinued or dropped out of the study, along with the reasons for their discontinuation or dropout will be listed.

[Variables]

Subject identification code, date of enrollment, date of discontinuation or dropout, reason for discontinuation or dropout.

## 7. Participant background

Descriptive statistics for the following variables will be calculated for each group. In addition, a list of the following variables of participant background will be prepared.

[Variables]

Categorical data:

Gender, race, comorbidities, medical history, smoking status, history of falls within 3 months prior to enrollment, level of care required, prescription drug information, current medical history (name of diagnosis), index disease

Continuous data:

Age at admission, height at admission, weight at admission, BMI at admission, vital signs at admission (blood pressure, pulse rate, temperature), laboratory results at admission (serum creatinine level, serum sodium level, serum potassium level, eGFR, pO2, pCO2)

## 8. Primary endpoint

### 8.1 Time to rehospitalization, unscheduled visit, or all-cause death

#### 8.1.1 Estimation of Survival Functions

Survival function of the time until rehospitalization, unscheduled visit, or all-cause death will be estimated using the Kaplan-Meier method for each group.

#### 8.1.2 Event rate

Survival rate and its 95% confidence interval at the following time points will be calculated using the survival function estimated in 8.1.1.

[Time point]

6 months

12 months

#### 8.1.3 Between-group comparison

Group comparisons will be made using stratified log-rank tests with stratified age groups (65-74, 75-84, 85+) as the strata.

#### 8.1.4 Hazard ratio

The hazard ratios and 95% confidence intervals for the intervention group compared to the usual care will be calculated using a Cox regression model with the time to rehospitalization, unscheduled visit, or all-cause death as the outcome variable and the allocation group and age group as explanatory variables.

#### 8.1.5 Stratified hazard ratio

The baseline hazard will be stratified based on age group strata, and the hazard ratio and its 95% confidence interval will be calculated for the intervention group compared to the usual care using a Cox regression model with the time until rehospitalization, unscheduled hospital visit, or all-cause death as the outcome variable and the allocation group as the explanatory variable.

## 8.2 Time to rehospitalization

The same analysis as in 8.1 will be performed for time to rehospitalization.

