#### **(2) Statistical analysis methods**

Participants who can no longer be contacted during the follow-up will be treated as censored when they were last contacted. Discontinuation of the study participation will not be considered a termination, thus observation will continue.

For the primary endpoint analysis, a survival function will be estimated for each group using the Kaplan-Meier method, which will be used to estimate survival rates and 95% confidence intervals at 6 and 12 months. Group comparisons will be made using stratified log-rank tests (two-sided) with stratified age groups (65-74, 75-84, 85+) as the strata. The significance level is set at 0.05. The baseline hazard will be stratified based on age group strata, and the hazard ratio and its 95% confidence interval will be calculated for the intervention group compared to the usual care using a Cox regression model with the time until rehospitalization, unscheduled hospital visit, or all-cause death as the outcome variable and the allocation group as the explanatory variable.

The same analysis as above will be performed for each of the time to rehospitalization, unscheduled visits, and all-cause mortality, which comprise the primary composite endpoint. The planned statistical tests are unadjusted for the multiplicity.

Subgroup analysis of the primary endpoint will be performed for each index disease (heart failure, pneumonia, diabetes, stroke, urinary tract infection) and drug class (antiplatelet/anticoagulant,

antihypertensive, antidiabetics, sedatives). The 12-month survival rate will be estimated for each subgroup by group and evaluated to see if the difference between groups is in the same direction as the overall analysis.

Details of the analysis methods for secondary endpoints and safety endpoints will be defined in a separate statistical analysis plan.

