### 8.3 Time to unscheduled hospital visit

The same analysis as in 8.1 will be performed for time to unscheduled hospital visit.

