#### 8.5.2 Time to rehospitalization

The same analysis as in 8.5.1 will be performed for time to rehospitalization.

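### Rehospitalisation alone and unscheduled visit alone are summarised by Kaplan-Meier with no rule for prior death; if deaths are censored, the reported event rates overstate the actual risk, probably modestly

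*Combined protocol and SAP*

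**What the plan says.** Protocol section 14(2) carries the composite analysis over to its parts: "The same analysis as above will be performed for each of the time to rehospitalization, unscheduled visits, and all-cause mortality". The SAP repeats this in 8.2 ("The same analysis as in 8.1 will be performed for time to rehospitalization") and 8.3 ("The same analysis as in 8.1 will be performed for time to unscheduled hospital visit").

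The estimator carried over is in SAP 8.1.1: "Survival function of the time until rehospitalization, unscheduled visit, or all-cause death will be estimated using the Kaplan-Meier method for each group". SAP 8.1.2, which is headed as an event rate, adds: "Survival rate and its 95% confidence interval at the following time points will be calculated using the survival function estimated in 8.1.1". The time points are 6 and 12 months. Sections 8.1.3 to 8.1.5 add the age-stratified log-rank test and two Cox models.

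The subgroup sections work the same way. SAP 8.5.2 reads "The same analysis as in 8.5.1 will be performed for time to rehospitalization"; 8.5.3 matches it for unscheduled visits, and 8.6 applies the method of 8.5 to drug classes. Section 8.5.1 contains only Kaplan-Meier curves and a 12-month rate with its interval.

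SAP 4.3 measures time to rehospitalisation and time to unscheduled visit from random allocation. Death belongs to neither event. The one censoring rule, in protocol section 14(2), concerns loss of contact: "Participants who can no longer be contacted during the follow-up will be treated as censored when they were last contacted". Neither document mentions competing events or cumulative incidence.

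**The concern.** A patient who dies without having been rehospitalised can no longer be rehospitalised. If that death is treated as censoring, Kaplan-Meier in effect assumes that the patient would have gone on to be rehospitalised at the same rate as the survivors. One minus Kaplan-Meier then describes a hypothetical population without deaths, and it exceeds the proportion of patients who actually have the event. SAP 8.1.2 reports the survival side of the curve, so the event-free rate is too low and its complement, the event rate, too high.

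Deaths before a component event are to be expected here. Patients are inpatients aged 65 or over on at least five drugs, and only a life expectancy under one month excludes them. The clock starts at allocation during the index stay, and death during that stay is itself a secondary endpoint; such a patient cannot be rehospitalised.

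What is at stake is the description of the components. Rehospitalisation and unscheduled visit are secondary endpoints in protocol section 7, and their rates will be used to explain the composite. In the component subgroup sections there is no hazard ratio or test, so the affected rates and curves are the only result.

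**Working it through.** **The plan's own figure.** The documents state no component rate and no mortality rate, so there is no figure to reproduce. The only anchor is the planned 12-month composite rate in protocol section 15 and SAP 2.2: 30% with the intervention and 40% in control. Patients who are rehospitalised and patients who die without prior rehospitalisation are separate groups, and both lie inside the composite. Their sum therefore cannot exceed the composite rate. I use 30% and 40% as caps.

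**Formulas**, assuming constant hazards. Let *r* be the true 12-month cumulative incidence of rehospitalisation, *d* that of death without prior rehospitalisation, and *t* the time in years.

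- Total hazard: H = −ln(1 − r − d)
- Rehospitalisation hazard: h = H × r/(r + d)
- One minus Kaplan-Meier, deaths censored: 1 − exp(−h·t)
- True cumulative incidence: [r/(r + d)] × [1 − exp(−H·t)]

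**Worked case**, r = 20%, d = 10%: H = −ln 0.70 = 0.3567; h = 0.3567 × 2/3 = 0.2378; 1 − exp(−0.2378) = 21.2%, against a true 20%.

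| r / d (assumed) | Sum | 1 − KM, 12 months | Excess, 12 months | Excess, 6 months |
|---|---|---|---|---|
| 25% / 5% | 30% | 25.7% | 0.7 points | 0.2 points |
| 20% / 10% | 30% | 21.2% | 1.2 | 0.3 |
| 15% / 15% | 30% | 16.3% | 1.3 | 0.4 |
| 30% / 10% | 40% | 31.8% | 1.8 | 0.5 |
| 25% / 15% | 40% | 27.3% | 2.3 | 0.7 |
| 20% / 20% | 40% | 22.5% | 2.5 | 0.7 |

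Varying the split with the sum fixed, the largest 12-month excess is about 1.3 points at a 30% sum and 2.5 points at a 40% sum, reached when the two groups are about equal in size. The same formulas apply to unscheduled visits.

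**Sensitivity to constant hazards.** Take a 12-month one-minus-Kaplan-Meier rate of 30% and 12-month mortality of 10%, acting independently. The sum is 1 − 0.70 × 0.90 = 37%, within the control cap. Constant hazards give a true cumulative incidence of 28.6%, an excess of 1.4 points. If half the deaths fall in the first month, simulation gives 27.9%, an excess of 2.1 points. Early deaths widen the gap.

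**Unequal mortality between arms**, looked at in two ways:

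- *Equal true incidence.* With r = 20% in both arms and d = 10% versus 20%, Kaplan-Meier gives 21.16% versus 22.54%, a gap of 1.4 points. The hazards h are 0.2378 and 0.2554, so the rate of rehospitalisation among patients still alive does differ.
- *Equal hazards.* With h = −ln 0.80 in both arms and mortality of 10% versus 20%, Kaplan-Meier gives 20.0% in both. The true incidence is 19.0% versus 18.0%, so the excess is 1.0 and 2.0 points.

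In both, the arm with more deaths has the larger excess.

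**The case against.** The strongest case on the other side has four parts.

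- *The plan never says that deaths are censored.* True. What is documented is a missing rule; the overstatement follows on the ordinary reading of applying 8.1 unchanged. The rule must be stated in any case.
- *The effect is small.* With about 212 analysed per arm (423/2), a 95% interval for a difference between two rates near 30% is about ±1.96 × √(2 × 0.30 × 0.70/212) = ±8.7 points. An excess of 1 to 2.5 points is well inside that. This limits the importance of the point, but sampling error does not remove a bias of known direction. A reader might infer an excess of 5 points or more. Under constant hazards that needs rehospitalisation and prior death to total well above the planned 40%, which the documents do not support.
- *The tests and hazard ratios are sound.* This stands. With deaths censored, the log-rank test and Cox model compare cause-specific hazards validly. A reader might infer that the primary result is biased too; it is not, because death is an event in the composite (8.1) and in all-cause death (8.4).
- *No false treatment difference has been shown.* This also stands. A reader might infer that unequal mortality makes Kaplan-Meier produce a spurious difference between arms. Whether a difference is spurious depends on the estimand. Equal incidence with unequal deaths means that the hazards really differ. With equal hazards, it is the cumulative incidence that makes the arm with more deaths look better. For that reason neither summary should be shown without the death result.

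**Conclusion.** The point holds for the absolute component rates and curves in SAP 8.2, 8.3, 8.5.2, 8.5.3 and the matching parts of 8.6, and for the component sentence in protocol section 14(2). It should be corrected, but it does not threaten the primary analysis.

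The direction is certain if deaths are censored and some occur before the component event. The size is not fixed by the documents. The limits of about 1.3 and 2.5 points at 12 months rest on constant hazards and on the planned composite rates; higher event rates or early deaths would raise them. The 6-month figures of roughly 0.2 to 0.7 points are the cases tabulated, on the same assumptions.

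**What to change.** 1. State in the SAP how a death before the component event is handled.
2. In 8.2, 8.3, 8.5.2, 8.5.3 and the matching parts of 8.6, replace the Kaplan-Meier rates and curves by Aalen-Johansen cumulative incidence, with death as the competing event.
3. Keep the age-stratified log-rank test and the Cox models in 8.2 and 8.3, labelled as cause-specific, and show all-cause death beside them.
4. Leave 8.1 and 8.4 unchanged.
5. Make the matching change to protocol section 14(2), or record the departure. Changing the SAP alone would create another mismatch between the two documents, the kind of problem that led to SAP version 1.2.
6. Date the change and declare it as made after analysis, because the revision history shows that version 1.2 was itself written once the analysis had been run.

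No new data are needed: SAP 8.7 already lists the dates of enrolment, rehospitalisation, unscheduled visit and death. The cost is a little extra analysis work and a post-hoc label on the new rates.

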### 8.3 Time to unscheduled hospital visit

The same analysis as in 8.1 will be performed for time to unscheduled hospital visit.

### 8.4 Time to all-cause death

The same analysis as in 8.1 will be performed for time to all-cause death.

### 8.5 Subgroup analysis according to index diseases

Subgroup analysis based on the index diseases listed below will be performed for the following analyses.

[Index disease]

Heart failure

Pneumonia

Diabetes mellitus

Cerebral infarction

Urinary tract infection

#### 8.5.1 Time to first occurrence of any of rehospitalization, unscheduled visit, or all-cause death

##### 8.5.1.1 Estimation of Survival Functions

Survival function of the time until rehospitalization, unscheduled visit, or all-cause death occurs will be estimated by the Kaplan-Meier method for each group.

##### 8.5.1.2 Event rate

The survival rate and its 95% confidence interval at 12 month will be calculated using the survival function estimated in 8.5.1.1.

#### 8.5.2 Time to rehospitalization

The same analysis as in 8.5.1 will be performed for time to rehospitalization.

#### 8.5.3 Time to unscheduled hospital visit

The same analysis as in 8.5.1 will be performed for time to unscheduled hospital visit.

#### 8.5.4 Time to all-cause death

The same analysis as in 8.5.1 will be performed for time to all-cause death.

## 8.6 Subgroup analysis according to index drug class

The analysis will be conducted in the same method as in 8.5, with subgroups based on the use of the following drug classes at baseline: time to any occurrence of rehospitalization, unscheduled visit, or all-cause mortality; time to rehospitalization; time to unscheduled visit; time to all-cause death.

[Index drug class]

Antiplatelets/anticoagulants

Antihypertensives

Antidiabetics

Sedative

## 8.7 List of variables related to primary endpoint

The following items related to the primary endpoint will be listed.

[Variables]

Date of enrollment, date of rehospitalization, date of unscheduled visit, date of all-cause death, cause of death, presence of index disease (heart failure, pneumonia, diabetes, stroke, urinary tract infection), presence of index drug class (antiplatelets/anticoagulants, antihypertensives, antidiabetics, sedatives).

## 9. Secondary endpoints

### 9.1 Death during initial hospitalization

Survival function for time to death during the initial hospitalization will be estimated using the Kaplan-Meier method for each group. In addition, differences in survival functions between groups will be compared using the Log-rank test.

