### **4. Participants**

#### **(1) Inclusion Criteria:**

Patients who meet all of the following criteria will be considered eligible.

1. Medical inpatients admitted to the internal medicine departments of Kawasaki Municipal Tama Hospital (general internal medicine, gastroenterology&hepatology, cardiology, pulmonology, endocrinology, nephrology, and neurology) at Kawasaki Municipal Tama Hospital;
2. Aged 65 years or older;
3. Taking five or more regularly prescribed medications;
4. Predicted length of hospital stay after admission: 1 week or longer;
5. Patients who are deemed eligible to take the drug orally by their attending physician;
6. Patients who have been fully informed of the study and who have given their or their surrogate's free and voluntary written consent based on a thorough understanding of the study.

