#### **(2) Exclusion Criteria:**

Patients will not be included in the study if the following apply.

1. Attending physicians disagreeing to study participation;
2. Life expectancy of less than 1 month based on their attending physician's clinical judgement.

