### **(3) Endpoints**

#### **<Primary endpoints>**

All-cause deaths, unscheduled visits, and rehospitalizations up to 12 months after allocation will be confirmed

by telephone survey every 2 months, including specific dates, referring to the entries in the follow-up diary provided in advance. A hospital transfer is considered to be a continued hospitalization, and a rehospitalization is defined as "hospitalization due to any new event". If necessary, we will request information from the patient's primary care institution, primary care pharmacy, home nursing station, after making a request for research cooperation in advance.

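### SAP 9.1 analyses in-hospital death by Kaplan-Meier and an unstratified log-rank test without saying how discharge alive, a competing event, is handled

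*Combined protocol and SAP*

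**What the plan says.** Protocol section 7(2) lists death during the initial hospitalisation as a secondary endpoint. SAP 4.3 defines it as "Time to death from any cause occurring during the initial hospitalization, starting from the date of enrollment and random allocation". SAP 9.1 gives the whole analysis: "Survival function for time to death during the initial hospitalization will be estimated using the Kaplan-Meier method for each group", and "differences in survival functions between groups will be compared using the Log-rank test". The level comes from SAP 5.1: "Two-sided test with a significance level of 0.05 will be used for group comparison". SAP 9.1 names no day at which the curve is to be read, whereas SAP 8.1.2 does so for the primary endpoint. It plans no proportion, no cumulative incidence and no stratification.

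The only censoring rule in either document is in protocol section 14(2): "Participants who can no longer be contacted during the follow-up will be treated as censored when they were last contacted". Discharge alive is not mentioned there, in SAP 4.3 or in SAP 9.1. On transfers, protocol section 8(3) states: "A hospital transfer is considered to be a continued hospitalization". That sentence belongs to the definition of rehospitalisation and is not repeated for this endpoint.

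Age group is the randomisation factor (protocol section 6(5)). It stratifies the log-rank test for the primary endpoint (SAP 8.1.3) and, by cross-reference, the tests for rehospitalisation, unscheduled visit and all-cause death (SAP 8.2 to 8.4). SAP 9.1 has the only log-rank test in the plan without strata.

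**The concern.** The event can happen only while the patient is still in the initial stay. Discharge alive therefore does not hide a later event, as ordinary censoring does. It rules the event out.

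Kaplan-Meier with censoring at discharge gives the mortality that would be seen if nobody ever left hospital, estimated from a shrinking group of long-stay patients. A reader will take the curve as the share of patients who died in hospital, and it is not that. The log-rank test on the same data compares death rates per day in hospital. Two arms with the same proportion of deaths but different lengths of stay then differ on the test.

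Length of stay could plausibly differ here. The protocol's background cites a systematic review in which STOPP/START interventions were associated with shorter stays, and STOPP/START is part of this intervention. With equal deaths, the arm with shorter stays would look worse.

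**Working it through.** **The plan's own figure.** There is none to reproduce. The documents give no in-hospital mortality for this endpoint and no expected stay beyond the inclusion criterion "Predicted length of hospital stay after admission: 1 week or longer". The nearest text on mortality is the exclusion of patients with "Life expectancy of less than 1 month". Mortality and stay below are therefore assumptions.

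**Step 1. Overstatement if patients are censored at discharge.** Let p be the share who die in hospital, M the median time from randomisation to leaving hospital (dead or alive), and t the day. With constant hazards the total exit rate is ln2/M and the death rate is p × ln2/M, so

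- one minus Kaplan-Meier = 1 − exp(−p × ln2 × t/M)
- true cumulative incidence = p × (1 − exp(−ln2 × t/M))

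With p = 5% and M = 18 days:

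| Day | 1 − Kaplan-Meier | True cumulative incidence | Ratio |
|---|---|---|---|
| 14 | 2.7% | 2.1% | 1.3 |
| 30 | 5.6% | 3.4% | 1.6 |
| 60 | 10.9% | 4.5% | 2.4 |
| 90 | 15.9% | 4.8% | 3.3 |

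For example, at day 60: 1 − exp(−0.05 × 0.693 × 60/18) = 10.9%, and 0.05 × (1 − exp(−0.693 × 60/18)) = 4.5%.

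**Step 2. Range.** With p from 3% to 8% and M from 14 to 25 days, the day-90 value is 7% to 30%, against a true 2.8% to 7.9%. With p from 2% to 10% and a mean remaining stay of 10 to 30 days, the ratio is 1.2 to 1.8 at day 14, 1.5 to 3.1 at day 30 and 2.7 to 8.2 at day 90.

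**Step 3. A different shape of stay.** A simulation with 250 per arm, a lognormal stay (median 14 days, sigma 0.7) and 5% deaths gives 3.3% against 2.5% at day 14, 9.0% against 4.3% at day 30, and 23.2% against 5.0% at day 90. The direction and the growth with time do not depend on constant hazards.

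**Step 4. The log-rank test.** Under constant hazards the in-hospital death rate is p × ln2/M. With p equal in both arms and median stays of 15 and 18 days, the apparent hazard ratio is 18/15 = 1.2 against the arm with the shorter stay. In simulation with 5% in-hospital mortality in both arms, the nominal 5% test rejects as follows:

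| Median stays (days) | Rejection rate, censored at discharge |
|---|---|
| 14 and 14 | 5.4% |
| 12 and 14 | 8.0% |
| 10 and 14 | 18.0% |

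**Step 5. The other reading.** If discharged patients stay in the risk set as event-free to 12 months, one minus Kaplan-Meier equals the crude in-hospital proportion (5.0% against 5.0% in the simulation). The log-rank test then rejects 4.3% to 4.9% of the time in the same three settings.

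**The case against.** A reader might infer that the SAP censors at discharge and so will overstate in-hospital mortality several-fold. The documents do not support that as fact.

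- **Censoring at discharge is not written anywhere.** The stated rule covers loss of contact only. Participants are followed for 12 months whether or not they have left hospital, and observation continues after discontinuation. An analyst could reasonably keep discharged patients at risk, and then there is no bias. This stands, and it makes the point conditional.
- **The size depends on where the curve is read.** The ratio is below 2 up to day 14 and becomes several-fold only in the late tail. In the base case about 25 of 250 patients per arm are still in hospital at day 60 and about 8 at day 90. SAP 9.1 asks for no rate at any day. This stands too.
- **The log-rank test is not invalid.** With censoring at discharge it compares in-hospital hazards, which is a legitimate but different question from the risk of dying in hospital. With 25 deaths (5% of 500), a hazard ratio of 1.2 shifts the test statistic by (√25/2) × ln 1.2 = 0.46, which raises rejection only from 5% to about 7%. Larger distortion needs a larger difference in stay, and the documents predict none for this trial.
- **A proportion also depends on length of stay.** With an unchanged daily death rate, cutting the median from 18 to 15 days lowers the in-hospital proportion from 5.0% to 5.0% × 15/18 = 4.2%, which favours the shorter stay. This is correct, but the proportion does estimate the endpoint that the protocol names. It is a reason to read it beside all-cause death, which does not depend on discharge.

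The gap in the plan remains. Two analysts could both follow SAP 9.1 and, in the base case, show 4.8% or 15.9% at day 90 from the same patients.

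**Conclusion.** The point holds in conditional form. SAP 9.1 leaves the handling of discharge alive open. Under the usual choice, censoring at discharge, the curve overstates in-hospital death by about 1.3-fold at day 14, rising to 3.3-fold at day 90, and the test mixes length of stay with mortality. Those figures rest on an assumed 5% mortality, an 18-day median stay and constant hazards; other plausible inputs move them as shown. Under the alternative of keeping discharged patients event-free to 12 months, there is no bias.

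Independently of that choice, the test omits the age strata used in randomisation and in every other log-rank test in the plan, and no reason is given.

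This is one secondary endpoint. The primary analysis and the 12-month all-cause death analysis (SAP 8.4) are unaffected. It is an improvement at almost no cost, not a threat to the trial's main conclusion.

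**What to change.** Replace the analysis in SAP 9.1 by the number and proportion of analysed participants in each arm who died before discharge from the initial hospitalisation. Add an age-stratified (Mantel-Haenszel) risk difference with its 95% confidence interval. State in SAP 4.3 that transfer counts as continued stay for this endpoint as well.

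If a curve is wanted, use the cumulative incidence function with discharge alive as the competing event, and an age-stratified Gray test. This needs the discharge date, which is not among the items in protocol section 8(1) or SAP 8.7. Medications are recorded at discharge, so the date may exist, but its availability should be confirmed first. The proportion needs only whether death came before discharge.

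Report the result beside all-cause death over 12 months (SAP 8.4), with a sentence saying that any in-hospital measure depends on length of stay. The SAP revision history shows that version 1.2 followed the analysis, so a change made now should be labelled post hoc.

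The cost is one SAP paragraph and a few lines of R. The proportion needs no new data provided that the order of death and discharge is recorded.
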